## Abstract

**Introduction:**

Ovarian cancer (OC) is associated with non-specific symptoms such as bloating, making accurate diagnosis challenging: only 1 in 3 women with OC presents through primary care referral. National Institute for Health and Care Excellence guidelines recommends sequential testing with CA125 and routine ultrasound in primary care. However, these diagnostic tests have limited sensitivity or specificity. Improving accurate triage in women with vague symptoms is likely to improve mortality by streamlining referral and care pathways. The Refining Ovarian Cancer Test Accuracy Scores (ROCkeTS; HTA 13/13/01) project will derive and validate new tests/risk prediction models that estimate the probability of having OC in women with symptoms. This protocol refers to the prospective study only (phase III).

**Methods and analysis:**

ROCkeTS comprises four parallel phases. The full ROCkeTS protocol can be found at http://www.birmingham.ac.uk/ROCKETS. Phase III is a prospective test accuracy study. The study will recruit 2450 patients from 15 UK sites. Recruited patients complete symptom and anxiety questionnaires, donate a serum sample and undergo ultrasound scored as per International Ovarian Tumour Analysis (IOTA) criteria. Recruitment is at rapid access clinics, emergency departments and elective clinics. Models to be evaluated include those based on ultrasound derived by the IOTA group and novel models derived from analysis of existing data sets. Estimates of sensitivity, specificity, c-statistic (area under receiver operating curve), positive predictive value and negative predictive value of diagnostic tests are evaluated and a calibration plot for models will be presented. ROCkeTS has received ethical approval from the NHS West Midlands REC (14/WM/1241) and is registered on the controlled trials website (ISRCTN17160843) and the National Institute of Health Research Cancer and Reproductive Health portfolios.

Strengths and limitations of this studyROCkeTS conforms to the PROBE design for biomarker evaluation and STARD criteria for test accuracy studies.Stringent efforts to collect outcome data to prevent ascertainment bias.Inbuilt ultrasound quality control.Recruitment is at secondary care, so the population will be less heterogeneous than that is seen in primary care.

## Introduction

Ovarian cancer (OC) is the seventh most common cancer in women worldwide, with 239 000 new cases diagnosed in 2012.^1^ In the UK, OC has an annual incidence of 7116 women and causes 4271 deaths; the lifetime risk of developing OC is 1 in 54.^2^ Seventy per cent of patients will present at an advanced stage (stages III/IV). The International Cancer Benchmarking Project showed that the reason that OC survival in the UK is significantly lower than other western countries seems to be related to a lower proportion of patients receiving treatment and surviving the first year after cancer diagnosis and is likely due to a delay in diagnosis.^3^ Five-year survival rates are 43% overall but over 90% for early-stage tumours.^4^ High-grade serous is the most common histotype (80%). Worryingly, long-term survival from OC has remained static over the past decades at 30%.^2^

OC was previously considered a ‘silent killer’; it is now recognised that patients with OC suffer from a number of non-specific symptoms. These include abdominal bloating, distension, feeling full quickly and/or loss of appetite, pelvic/abdominal pain, increased urinary urgency and/or frequency, unexplained weight loss, fatigue or changes in bowel habit. These symptoms are very common.^5^
^6^ Interrogation of UK General Practice databases suggest that on average one in two women between the ages of 45 and 74 presents once a year to her general practitioner (GP)/primary care doctor with these symptoms. Abdominal bloating alone^5^
^6^ is documented in 16–30% of women presenting to GPs.^7^ Diagnostic challenges are considerable given (1) the low incidence of OC (a GP sees a woman with OC once in 3–5 years) and (2) the low positive predictive value (PPV) of symptoms (only 1 in 400–600 symptomatic women have OC).^8^
^9^ Unfortunately, these diagnostic challenges result in nearly 36% of women, subsequently diagnosed with OC, presenting to the GP with symptoms three or more times prior to diagnosis.^10^ Two large prospective studies of symptom-triggered testing for OC suggest that symptom-triggered testing using CA125 is likely to result in referral of a higher proportion of patients with resectable disease.^11^
^12^

The UK introduced symptom-triggered testing for OC in women with vague symptoms in 2011. National Institute for Health and Care Excellence (NICE) guidelines recommend sequential testing using serum CA125 followed by pelvic ultrasound scan (USS) in women (particularly aged ≥50) presenting to primary care with symptoms such as persistent abdominal distension/‘bloating’, feeling full and/or loss of appetite, pelvic/abdominal pain, increased urinary urgency and/or frequency, unexplained weight loss, fatigue or changes in bowel habit on a persistent or frequent basis.^13^ However, the NICE guidelines do not specify the type of ultrasound abnormalities that should prompt referral. Current tests have limited sensitivity with CA125 being elevated only in 40–50% of women with stage 1 OC in screening and presurgical studies.^14^
^15^ Once referred to secondary care, women with complex masses considered benign can undergo laparoscopic or conservative management, whereas women with malignancy who undergo surgery by trained gynaecological oncologists have the best outcome.^16^
^17^ Use of NICE guidelines in practice is extremely variable. A survey of 258 GPs reported that the majority would refer patients on the basis of raised CA125 even if the USS was normal.^18^ A recent audit revealed that the majority of referrals (90%) for suspected OC did not follow the guidelines. Referrals were heterogeneous with regard to which symptoms prompted these, what GPs considered to be abnormal CA125 level or abnormal USS.^19^ Two-thirds of women referred were premenopausal.^19^

Therefore, improved diagnostic tools in primary care and better presurgical triage in secondary care are likely to improve mortality in patients with OC. Optimal diagnostic pathways for premenopausal women with suspected OC/complex ovarian mass and raised CA125 also need to be defined. Ovarian cysts in premenopausal women are extremely common; however, it is important to recognise that about 1000 women under 50 will be diagnosed with OC in the UK annually.^2^

The National Institute of Health Research Health Technology Assessment programme commissioned ROCkeTS—‘Refining Ovarian Cancer Test accuracy Scores’ 13/13/01 (1 October 2014 and 30 September 2018)—which aims to identify, refine and validate tests and clinical risk scores (risk prediction models) that estimate the probability of having OC in postmenopausal and premenopausal women with symptoms, in primary and secondary care. The project comprises four phases/work packages: phase I—systematic reviews of existing risk prediction algorithms and biomarkers to detect OC; phase II—interrogation of data sets from two large OC trials: the screening trial UKCTOCS and the preoperative detection International Ovarian Tumour Analysis (IOTA) studies to derive or refine risk scores with biomarkers from the systematic review; phase III—a prospective study to validate new scores in women newly referred to secondary care with symptoms of OC and phase IV—a model of the diagnostic pathway across primary and secondary care. A cost consequence analysis of testing pathways will be delivered as part of ROCkeTS.

The full ROCkeTS protocol can be found at http://www.birmingham.ac.uk/ROCKETS.

The ROCkeTS project evaluates risk prediction models derived from conventional tests—symptoms, ultrasound variables and commercially available serum blood tests.

Phase III of ROCkeTS is a cross-sectional study aimed at establishing the accuracy of tests and prediction models for the diagnosis of prevalent OC. However, of necessity, the reference standard for a correct diagnosis is follow-up to 12 months, as the study is not restricted to women scheduled for immediate surgery. This is a diagnostic trial (not a screening trial) as women are symptomatic and referred to secondary care.

The phase III prospective study will recruit 2450 premenopausal and postmenopausal symptomatic women over 23 months (recruitment started in June 2015). Patients will be recruited through rapid access clinics, emergency departments or through routine clinic referrals, reflecting the heterogeneity of diagnostic routes for OC in the UK.

Recruited patients consent to complete a validated symptom questionnaire, donate a serum sample and undergo an USS scored as per the IOTA criteria. Standard care pathways are followed beyond this point. Patients are triaged to receive surgery or conservative management based on standard of care model risk of malignancy index (RMI) scores for postmenopausal women, using a threshold of 250 in postmenopausal women or as per local unit practice in premenopausal women. This threshold was selected by the funder as comparator as part of the commissioning brief as this is current standard of care in the UK.^13^ Participants and treating doctors will be blinded to the new biochemical serum test results which will be performed in batches as these are not part of standard clinical care. Outcome data will be collected from histology reports in women undergoing surgery or biopsy and from follow-up over 12 months of those managed conservatively. Symptom scores, serum biomarker tests and ultrasound data will be analysed at the end of follow-up to validate risk prediction models derived in phases I and II.

## ROCkeTS study design

### Aim of the study

To derive and validate risk prediction models that estimate the probability of having OC for women with symptoms suggestive of OC for postmenopausal and premenopausal women.To identify optimal risk thresholds of best models for the diagnosis of OC that can guide patient management.

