### Sample size

The diagnostic accuracy from models will be compared to the current tests recommended by NICE for primary and secondary care. The sample size has a 90% power to detect with 5% significance difference in accuracy between the existing test (RMI threshold 250) and the new model. Owing to the expected difference in performance in premenopausal and postmenopausal women, separate sample sizes have been calculated. Sample sizes are calculated assuming independence of test errors and interim analyses will confirm parameter assumptions.

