#### For postmenopausal women

The performance of RMI at threshold 250 is assumed to be 70% sensitive and 90% specific.^30^ One thousand and four hundred participants will be required to detect an increase in sensitivity of 10% (to 80%) and in specificity of 5% (to 95%). Based on a prevalence of 30% of OC in referred women (local audit figures), with sensitivity and specificity of RMI assumed to be 70% and 90%, a sample size of 1333 provides 90% power to detect an increase of sensitivity to 80% and specificity to 95% in paired data (conservatively assuming independence of test errors). Allowing for a loss to follow-up of up to 5%, this gives a final sample size of 1400.

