#### For premenopausal women

The performance of RMI is assumed to have a sensitivity of 72% and a specificity of 46% (local audit figures). The trial is powered to detect an increase in sensitivity of 10% (to 82%) and in specificity of 10% (to 56%). Prevalence of OC in premenopausal women referred to secondary care is about 10%.^19^ A sample size of 1000 will provide 100 OC events in which to build new models combining symptom and test data (adequate events to model 10 predictor variables) and will provide 90% power to detect an increase in specificity of 8% (from 46% for RMI to 54%). With a predicted loss to follow-up of up to 5%, the final sample size required is 1050 women.

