### Measures and costs

Validation of a risk prediction model and tests for estimating the probability of OC in women with suspected OC, key outcome measures include the accuracy of the tests and models in terms of their discrimination ability (eg, sensitivity, specificity) and calibration (observed vs predicted probabilities), and the identification of thresholds to guide patient management decisions.

Trial data collection will be undertaken prospectively for all participants in order to inform the costs for each pathway.

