### Analysis plan—test accuracy

We will report estimates of sensitivity, specificity, c-statistic (area under ROC curve), PPV and NPV of tests evaluated and a calibration plot for models evaluated. Also, in terms of our new model derived from phase II of the wider ROCkeTS project, its improvement over existing models will be summarised by comparing the c-statistic and the calibration. We will also summarise the net-reclassification index for each new predictor that existing models omitted.

The risk prediction models derived in phases I and II of the ROCkeTS project will each produce a predicted risk of OC by 12 months for all the individuals in our study. Therefore, we will compare the observed outcome at 12 months with this predicted risk. The calibration (in terms of calibration slope) and discrimination (eg, c-statistic) will be evaluated for the models derived and identified in phase I and phase II, and their performance will be compared to the existing RMI model. The calibration will be shown visually by grouping women into deciles ordered by predicted risk and considering the agreement between the mean predicted risk and the observed events in each decile. The aim was to use predefined models on the phase III data, so the bulk of phase III analysis will be external validation of predefined models. Where the data set is used to derive a new model, optimism will be reduced using shrinkage methods through internal validation.

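### Phase III is described both as validating predefined models and as finding optimal thresholds and building new models; the stated optimism remedy does not cover threshold or best-model choice, while RMI is fixed at 250

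*Protocol article*

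**What the plan says.** Two descriptions of phase III stand side by side.

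- **Selecting and building.** The aims are to derive and validate models and "To identify optimal risk thresholds of best models for the diagnosis of OC that can guide patient management" (Aim of the study). The key outcome measures include accuracy, calibration "and the identification of thresholds to guide patient management decisions" (Measures and costs). For premenopausal women, "A sample size of 1000 will provide 100 OC events in which to build new models combining symptom and test data" (Sample size).
- **Validating.** The end of the Introduction and the Design section say that the novel models come from phases I and II and are validated in phase III. Analysis plan—test accuracy adds that most of the phase III analysis is external validation of predefined models.

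The comparator is RMI at a cut-off of 250 (Comparator). The study is sized for "90% power to detect with 5% significance difference in accuracy between the existing test (RMI threshold 250) and the new model". No cut-off is given for the new models.

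On optimism, the analysis plan says: "Where the data set is used to derive a new model, optimism will be reduced using shrinkage methods through internal validation". Nothing is said about optimism from choosing a threshold, or from choosing the best of several predefined models.

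**The concern.** External validation protects a sensitivity or specificity estimate only if the cut-off, as well as the model, was fixed beforehand. Here one side of the powered comparison has a fixed cut-off. On the other side, the only route to a cut-off that the article names is an aim and outcome measure of phase III itself. Several candidates are in play: the IOTA simple rules, ADNEX and the models from phases I and II. Choosing the best performer or the best cut-off on the outcomes that then give its accuracy makes that accuracy look better than it will be in new patients. The stated remedy is triggered only when a new model is derived, so it would not reach this step.

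The thresholds are meant to guide patient management, so inflated accuracy would carry into that use. The premenopausal group is the more exposed, with about 100 cancers.

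**Working it through.** **1. The plan's own figure (postmenopausal).** Inputs from the Sample size section: "The performance of RMI at threshold 250 is assumed to be 70% sensitive and 90% specific"; the study is "to detect an increase in sensitivity of 10% (to 80%) and in specificity of 5% (to 95"%); prevalence 30%; paired data with independent errors; 90% power, 5% significance (taken as two-sided).

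For sensitivity, the discordant proportion is d = 0.70×0.20 + 0.30×0.80 = 0.14 + 0.24 = 0.38, and the difference is D = 0.10. McNemar sample size:

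n = (1.960√d + 1.282√(d − D²))² / D² = (1.960×0.616 + 1.282×0.608)² / 0.01 ≈ 395 cancers, and 395.1/0.30 = 1317 women.

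This is 1.2% below the stated 1333, so the figure is reproduced. The planned comparison is therefore sensitivity and specificity at a cut-off, which needs a cut-off for the new model.

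**2. Optimism from choosing the cut-off and the model on the same women.** Simulation with equal-variance binormal scores; 100 cancers and 900 non-cancers (premenopausal) or 400 and 933 (postmenopausal: 30% of 1333). The candidates are equally good, with correlation 0.5. The Youden-optimal cut-off and the best candidate are picked on the sample, and apparent accuracy is compared with true accuracy. The Youden rule, number of candidates, correlation and true c are assumptions; the article gives none of them.

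Two true c values use RMI's assumed accuracy, c = Φ((z_sens + z_spec)/√2):
- premenopausal (72%, 46%): Φ((0.583 − 0.100)/1.414) ≈ 0.63
- postmenopausal (70%, 90%): Φ((0.524 + 1.282)/1.414) ≈ 0.90

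Overstatement in percentage points:

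| Group, true c | Candidates | Sensitivity | Specificity |
|---|---|---|---|
| Premenopausal, 0.80 | 1 | 3.7 | 0.3 |
| Premenopausal, 0.80 | best of 3–5 | 6–7 | 0.7 |
| Premenopausal, 0.63 | 1 | 4.7 | 0.4 |
| Premenopausal, 0.63 | best of 3–5 | 6.9–8.0 | 0.7–0.8 |
| Postmenopausal, 0.90 | 1 | 1.2 | 0.4 |
| Postmenopausal, 0.90 | best of 3–5 | 2.1–2.5 | 0.9–1.0 |

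The targets are 10 points of sensitivity in both groups, 5 points of specificity postmenopausally, and 8 (powered) to 10 points of specificity premenopausally.

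**3. Best-model choice alone.** Postmenopausal, with each cut-off set to match RMI's specificity and models truly no better than RMI: one predefined model shows no bias and a nominally significant gain in about 5% of runs. Picking the best of 5 raises this to 19–25%, and the best of 10 to 31–33%.

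**4. What shrinkage does for a newly built model.** Logistic model, 10 predictors, 1000 women, 10% prevalence, two assumed predictor strengths. Uniform shrinkage multiplies the linear predictor by a constant (0.85 here), so the ranking of women and hence the ROC curve stay the same.

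| c-statistic | Apparent | After uniform shrinkage | True | Bootstrap-corrected |
|---|---|---|---|---|
| Weaker predictors | 0.701 | 0.701 | 0.660 | 0.668 |
| Stronger predictors | 0.817 | 0.817 | 0.801 | 0.800 |

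Uniform shrinkage alone does not correct discrimination; bootstrap internal validation largely does.

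**The case against.** The strongest reply is that the article already says that the models are predefined and that phase III mainly validates them. It also summarises improvement over existing models by the c-statistic and calibration, which need no threshold. This stands: for one predefined model, a threshold search cannot bias either measure. It does not settle the sensitivity and specificity comparison on which the sample size rests.

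A reader might go further in four ways that the documents do not support.

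- **That the RMI comparison will use thresholds chosen in phase III, so the gain is certainly overstated.** No section says so. The article leaves the route open, and the bias is conditional on it.
- **That shrinkage is the only remedy.** The text says shrinkage methods through internal validation. Internal validation can correct discrimination, and shrinkage methods other than a uniform factor can change the ranking. The article does not say that corrected sensitivity, specificity or c-statistic will be reported, but it does not exclude it.
- **That the bias is a large part of the premenopausal 8-point gain.** That target is in specificity, where the overstatement is under 1 point. Nearly all the optimism falls on sensitivity.
- **That any apparent advantage at a Youden cut-off is optimism.** In the postmenopausal simulation, a model no better than RMI showed a sensitivity gain of about 12 points. Most of that is a trade against specificity (true values about 82%/82% against 70%/90%).

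The full protocol or analysis plan may fix the thresholds, and leaving such detail to it would be no fault. What remains is in the article itself: aims and a sample-size rationale that do not sit with the validation design, and a remedy worded too narrowly for those aims.

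**Conclusion.** The point holds as a conditional one. The article gives phase III a selection and model-building role alongside a validation role, fixes the cut-off on RMI's side only, and limits its optimism remedy to newly derived models. If thresholds or best models are chosen on the women used for the RMI comparison, premenopausal sensitivity would be overstated by about 4 points for one predefined model and 6–7 for the best of 3–5, a material share of the 10-point target. Postmenopausal sensitivity would be overstated by about 1 and 2–3 points. Specificity would be overstated by under 1 point premenopausally and by up to about 1 point postmenopausally.

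These sizes rest on the assumptions listed in the check. Equally good candidates is an unfavourable case for selection bias, and a lower true c gives somewhat larger premenopausal figures. The direction, given same-data selection, does not depend on the exact inputs.

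**What to change.** 1. Reconcile the Aim of the study, Measures and costs, and the premenopausal sample-size paragraph with the Design and Analysis plan—test accuracy sections. State which models are validated and which, if any, are built in phase III.
2. Lock each predefined model together with its risk threshold before phase III outcomes are joined to index-test data. Base the sensitivity and specificity comparison with RMI 250 on these locked pairs.
3. Label as exploratory any model or threshold chosen on phase III data. Report it with bootstrap internal validation that repeats both the model choice and the threshold search in every resample, giving optimism-corrected c-statistic, sensitivity and specificity as well as shrunken coefficients.

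The cost is a change of wording, some computing, and slightly lower reported accuracy for data-driven models. Recruitment and data collection do not change.

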### Design

The ROCkeTS study is a single-arm prospective cohort diagnostic test accuracy study to evaluate existing and novel risk prediction models for premenopausal and postmenopausal women with symptoms.

A test accuracy study is different from an effectiveness study in that randomisation of participants is not involved. It is designed to generate a comparison of measurements obtained by tests under investigation (index tests) with those obtained from current standard of care tests (comparator test) against a reference standard. In this way, the accuracy of any new ‘index’ tests can be estimated. A reference standard is a test that confirms or refutes the presence or absence of disease beyond reasonable doubt. Therefore, it is sometimes also known as the ‘gold standard’. In this study, as per standards of diagnostic test evaluation, estimates of sensitivity, specificity, c-statistic (area under receiver operating curve (ROC) curve), PPV and negative predictive value (NPV) of tests evaluated and a calibration plot for models evaluated will be presented.

Here, the reference standard will be histology of tissues taken from patients who proceed to surgery or biopsy or follow-up using structured templates at a minimum of 12 months after presentation. The accuracy of the index test will be compared against that of the comparator test, the existing standard risk prediction score RMI. This index is an algorithm combining menopausal status, CA125 and ultrasound features and is standard of care in the UK.^20^ In ROCkeTS, the index test (novel risk prediction models) will be derived in phases I and II and validated in phase III. We will identify biochemical markers, symptom indices and USS as likely components of a novel risk prediction model, as these may be implemented across primary and secondary care. Therefore, we will collect symptom questionnaires, blood and USS data in the study to be analysed and validated at the end of the study.

